###  Outcome Measures

The primary outcome measure is the HAMD-17 and BDI-II. Evaluation timelines are set as: before treatment, and the second, fourth, and sixth weeks of the treatment. HAMD-17 and BDI-II are widely used in the diagnosis and outcome evaluation of depression. The range of the HAMD-17 score is 0 to 52, with 25 scores or more indicating severe major depressive disorder, 18–24 scores indicating moderate, 7–17 scores indicating patients may have mild depression, and 0–6 scores indicating normal (36). The range of the BDI-II score is 0 to 63, with 29–63 scores indicating severe major depressive disorder, 20–28 scores indicating moderate, 14–19 scores indicating mild, and 0–13 scores indicating normal. The secondary outcome measures are SDS, SAS, and PSQI. The range of the SDS standard score is 0 to 100, with 72 scores or more indicating severe major depressive disorder, 63–72 scores indicating moderate, 53–62 scores indicating mild, and 0–53 scores indicating normal. The range of the SAS standard score is 0 to 100, with 70 scores or more indicating severe anxiety, 61–70 scores indicating moderate, 50–60 scores indicating mild, and 0–50 scores indicating normal. The range of the PSQI score is 0 to 15, where a lower score indicates better sleep quality. A score of 11–15 indicates poor quality of sleep, and a score of 0–5 indicates good quality of sleep (37). Evaluation time points are as follows: before treatment, and the second, fourth, and sixth weeks of the treatment, and a follow-up period. Participants will be followed up at 3, 6, and 12 months after treatment and will complete the SDS, SAS, and PSQI. In addition, functional MRI (fMRI) is an optional test under the attending physicians' supervision and instruction or depending on the patient's self-willingness. The fMRI, if included, will be performed in the resting state before the treatment and at the sixth week of treatment (38). The detailed procedures and parameters of fMRI are provided in **Supplementary File 1**. Also, the patient's blood samples and feces will be obtained twice before and after the treatment and will be used to build a biological sample bank, which could help with the research protocol moving forward.

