**Discussion:**

This study intends to conduct a multicenter randomized controlled trial to compare the effectiveness among EA, counseling and the combined therapy in the treatment of patients with sub-threshold depression, and to further study the mechanisms of effect.

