### Trial Objective

We suspect that EA could alleviate the clinical symptoms of patients with sub-threshold depression as well as counseling. If EA is not only the placebo, the combination therapy will have a better effect, and may reduce the risk of conversion from mild to severe, as well as help determine whether patients with sub-threshold depression will need multiple therapies in the future. If acupuncture does no effect, the combination group will have the same clinical effect as the counseling group. Therefore, the objective of this trial is to evaluate the effectiveness of sub-threshold depression treatment by comparing the effects among EA, counseling, and combination therapy, as well as to further study the mechanism of EA and counseling.

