### Blinding

As a single-blinded trial, only outcome evaluators and statistical analysts will be blinded to treatment group. Evaluators and statistical analysts will not be allowed to participate in the treatment process of subjects and will be forbidden from knowing the grouping of subjects. Trial grouping information will be open to subjects, physicians, and data collectors. The analysts will generate a randomized sequence, only known by him or her, to allocate subjects accordingly to ensure the randomization of the grouping. The analyst will be responsible for the preservation and confidentiality of information and data and will prepare a backup of both electronic devices and paperwork. Special personnel will be in charge of those data and documentation. In addition, to ensure strict implementation of the blinded method in the test and reduce the bias of conclusions, physicians (psychologists and acupuncturists), outcome evaluators, data collectors, and statisticians will all be independent of each other and will have no communication during the test.

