### Randomization

Independent statisticians will use the block randomization method with SAS version 9.4 (SAS Institute. Inc., Cary, NC) to create a randomization table for each hospital. Randomization numbers will be sealed in opaque, sequentially numbered envelopes, and sent to each participating hospital (26). Random number envelopes will be kept in a double locker. If the participant meets the inclusion criteria and voluntarily signs the informed consent, the clinical research coordinator will send the sealed random number envelopes to the physician in order, who will open the envelope and allocate the qualified participants to the EA group, counseling group, and combined therapy group according to the random number.

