EA has been widely used to treat different psychiatric conditions, including depressive disorder (43). The putative antidepressant actions of EA are believed to involve modulation of hormones, neurotransmitters, and/or cytokines (25). Le et al. also found that EA could regulate the hypothalamus-pituitary-adrenal cortex axis, influence the hippocampus, and affect the dopaminergic and/or serotonergic systems to exert antidepressive activity (44). To date, few studies have been designed and conducted to investigate EA for sub-threshold depression. The goal of this RCT is to collect comparable data as well as to assess the usefulness, advantages, and effectiveness of EA treatment, in comparison to and in combination with counseling for alleviating sub-threshold depression. According to the main treatment principles of regulating the Governor Vessel with acupuncture, we have selected acupoints GV20 and GV29 in GV for EA to improve the curative effect for treating sub-threshold depression. In terms of imageology, EA at acupoint GV20 was previously found to modulate the default pattern network for patients with depression (45). We chose GV20 and GV29, and the bilateral acupoints GB13, because their stimulating area includes the prefrontal cortex. Prefrontal lobe dysfunction is pathophysiologically linked to depression (46). Previous studies confirmed that transcranial direct current stimulation of the prefrontal cortex is a method of treating depression (46, 47). We deduced that the location of our EA could also treat the subthreshold depression by stimulating the dorsolateral prefrontal cortex. The fMRI is a non-invasive test, and it can clearly show the brain area we want to observe (48). It is often used in depression or subthreshold depression studies to determine the efficacy (49, 50). Therefore, if the participants choose to perform fMRI, fMRI will be performed in the resting state before the treatment and at the sixth week of treatment (38).

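### Entry to fMRI, the only mechanism measure read within the trial, is discretionary while allocation is open, so the scanned subgroups can be selected differently by arm

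*Protocol article*

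**What the plan says.** Mechanism is an aim in the Abstract, the Introduction and the Trial Objective section. The last sets out to evaluate effectiveness "as well as to further study the mechanism of EA and counseling".

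Under Outcome Measures, every primary and secondary outcome is a clinical scale. Two biological items follow:

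- **fMRI.** It is described this way: "functional MRI (fMRI) is an optional test under the attending physicians' supervision and instruction or depending on the patient's self-willingness". On timing: "The fMRI, if included, will be performed in the resting state before the treatment and at the sixth week of treatment". The main Discussion section repeats the voluntary basis: "if the participants choose to perform fMRI".
- **Blood and feces.** These are taken before and after treatment and "will be used to build a biological sample bank, which could help with the research protocol moving forward".

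On knowledge of the arm, the Blinding section states: "Trial grouping information will be open to subjects, physicians, and data collectors". Under Randomization, the envelope passes after consent to the physician, "who will open the envelope and allocate the qualified participants to the EA group, counseling group, and combined therapy group".

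**The concern.** An optional imaging sub-study is ordinary. If participants opt in before randomisation, the scanned group may be unrepresentative, but the arms within it are still randomised at entry. If they opt in once the arm is known, the choice can depend on the arm, and the people scanned under EA, counseling and combination may be different kinds of people.

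The article gives two routes into scanning, and both run through someone who knows the allocation. There is also a plausible reason for interest to differ by arm: the Discussion proposes that EA works by stimulating the prefrontal cortex, which makes a brain scan a natural companion to EA and less obviously so to counseling.

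At stake is the mechanism aim. A difference in fMRI change between arms could reflect who was scanned rather than what the treatment did, and a larger sample would not remove that.

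**Working it through.** **1. Is fMRI the only mechanistic measure read within the trial?** The ranked outcomes are HAMD-17, BDI-II, SDS, SAS and PSQI, all clinical scales. Blood and feces go to a bank for later research. That leaves fMRI.

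**2. Can the scan decision follow allocation?** The sequence under Randomization is eligibility, consent, envelope, treatment. The first scan is tied only to the start of treatment, so the interval between envelope and first session is open. Nothing in the article places the decision before that interval, and both deciders know the arm during it.

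**3. Does the stated sample size help?** The one figure given is 46 per group, based on HAMD-17. A one-way ANOVA with means 5.7, 5.26 and 3.4, pooled SD √[(3.13² + 3.11² + 2.97²)/3] = 3.07, α = 0.05 and power 0.90 needs 42 per group. Allowing 10% dropout, 42/0.9 = 46.7, or 47. The stated 46 is reproduced to within one per group. It does not size the fMRI subset.

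**4. How large could the bias be?** All inputs here are assumptions. Let U be a standardised prognostic factor correlated ρ with the imaging change, with no true treatment effect. Bias in SD units = ρ × (mean U among the scanned in one arm − mean U among the scanned in the other). If the log-odds of being scanned are 0.5·U, uptake is 50% and mean U among the scanned is 0.236. With slope −0.5 it is −0.236, and with slope 0 it is 0. With 46 × 0.5 = 23 scans per arm, the standard error is √(2/23) = 0.295.

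| Uptake rule in the two arms | Bias, ρ = 0.3 | Bias, ρ = 0.5 | Type I error (ρ = 0.3; 0.5) |
|---|---|---|---|
| Same rule in both | 0 | 0 | 5%; 5% |
| Slope 0.5 against 0 | 0.07 | 0.12 | 5.7%; 6.9% |
| Slope 0.5 against −0.5 | 0.14 | 0.24 | 7.7%; 12.6% |
| Slope 0.5 in both, uptake 72% against 28% | 0.06 | 0.11 | 5.4%; 6.2% |

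The last row gives the absolute size of the bias. It shows that different uptake rates alone, under the same dependence on U, also produce some bias.

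**5. What could the subset detect?** No uptake is stated. Suppose 20%, 30% or 50%: 46 × 0.2 = 9.2, 46 × 0.3 = 13.8 and 46 × 0.5 = 23, so about 9, 14 or 23 per arm. A two-sample t-test (two-sided 5%, 80% power) then detects 1.41, 1.10 or 0.84 SD. At full uptake (46) it detects 0.59 SD. These figures describe precision under assumed uptake and do not measure the selection bias.

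**6. Is there a second filter?** The first scan precedes treatment, so opting in cannot depend on response. The second scan is at week 6. The Combination Therapy Group section describes participants being stopped after week 2 because of insufficient effect or worsening. Who reaches the second scan can therefore depend on response, and through it on arm, whenever the opt-in was recorded.

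**The case against.** The strongest reply is that the article is silent on when the choice is made, and unseen documents may settle it. Supplementary File 1 holds the fMRI procedures, consent forms are not shown, and consent precedes the envelope, so an opt-in at consent fits the text. It is also fair that the Statistical Analysis section specifies no between-arm fMRI comparison, that the article already places fMRI outside its ranked outcomes, and that the biases in step 4 are well below the detectable differences in step 5.

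Much of this stands, and it rules out some stronger readings:

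- A reader might infer that the scanned groups are in fact selected by arm. Selection of some kind is certain, but selection that differs by arm is only a risk the wording allows.
- A reader might infer that mechanism has equal standing with effectiveness. It is listed alongside, but the outcomes and the sample size are wholly clinical.
- A reader might infer that the scanned subset will be small. No uptake is given.
- A reader might want the biobank reclassified. The article already describes it as a resource for future research.

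The reply does not dispose of the point. The article states the entry rule: the attending physician's instruction is a named route, and that physician knows the arm. The rule itself permits arm-dependent entry, whatever a supplement adds on timing. A purely within-arm reading of the scans would avoid the bias, but it could not separate a treatment effect from change over time.

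**Conclusion.** The concern holds as a risk that the stated entry rule leaves open. If uptake depends on the arm, a between-arm fMRI comparison loses the protection of randomisation. The size is unknown, because uptake and its determinants are not stated. Under the assumptions in step 4 it runs from no bias (one rule in all arms) to about 0.24 SD, with a type I error of up to 12.6% instead of 5%. The larger values need opposite selection in the two arms and a correlation of 0.5.

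The HAMD-17 and BDI-II comparisons do not depend on scanning and are unaffected. The change is worth making because it is cheap and because the order of choice and allocation cannot be restored afterwards. If Supplementary File 1 or the consent form already fixes the choice before allocation, the timing part reduces to a cross-reference. The physician route and the week-6 losses would still need attention.

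**What to change.** - Record each participant's fMRI decision at consent, before the envelope is opened.
- Remove physician instruction after allocation as a way into the scanned group for this comparison.
- Analyse those who opted in before randomisation by assigned arm, and report their baseline features against those who declined.
- Report week-6 scan losses by arm with reasons, counting separately those stopped under the rule in the Combination Therapy Group section. Moving the opt-in does not cure these losses.
- Label the fMRI mechanism comparison exploratory where the aim is stated.

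The biobank text needs no change. The cost is one field on the consent or enrolment form and a short wording amendment. The downside is losing a few participants who would have agreed to scanning only after learning their arm.

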### Statistical Analysis

Statistical analysis will be performed by qualified statisticians in a blinded manner using Statistical Product and Service Solutions (SPSS) software (IBM Corporation, Version 21.0). An ITT analysis will be performed. The baseline comparability of the three groups will be assessed on demographic and clinical characteristics, as well as baseline data. Analysis of variance will be used to compare the mean changes between groups from baseline to each time point. The withdrawal of any subjects from clinical trials will be statistically described one by one. The missing data of a withdrawn patient will be randomly filled with the filling method based on the principle of multiple imputations (34). Continuous variables will be represented by mean ± standard deviation. The data before and after treatment in the group will be compared based on a paired *t*-test, and the comparison between groups will be performed using an independent sample *t*-test. When data are not normally distributed, a Wilcoxon rank sum test or Fisher's exact test will be performed. Multiple measurements of the same indicator at different times will use repeated measures data analysis of variance. Categorical variables will be expressed as frequency (%). Two-tailed *p* values < 0.05 will be considered as statistically significant. Safety will be assessed by adverse events and tabulations of adverse drug reactions and descriptive statistics will be performed. Age and intervention assessment are continuous variables, and their correlation will be analyzed using Pearson correlation coefficients. Treatment duration and gender are graded variables, and the spearman correlation coefficient will be used for the correlation analysis of the intervention assessment. To further evaluate the credibility of the blind method. We will evaluate the implementation of the blind method by trial participants' guesses about the allocation of treatment plans, that is, forcing evaluators and statistical analysts to guess the groups to which the subjects are assigned, and then calculate the Blinding Index Scale based on the guess results (39). In order to balance the heterogeneity of patients from different research centers, we will first analyze the differences between the clinical effects of different interventions in each subcenter. If the conclusions of the subcenters are consistent, there will be no central effect. If the conclusions of the sub-centers are inconsistent, a logistic regression analysis will be performed, and the center will be adjusted as a covariate to analyze the results of interventions and clinical assessment (40, 41).

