### Sample Size

Sample size estimation uses a completely random design to compare multiple sample means. Target sample size was estimated using the PASS11 version, 1-β = 0.9, α = 0.05. According to a previous study (27), the mean of HAMD-17 in the psychological counseling group was 5.7, and the standard deviation was 3.13; the mean of HAMD-17 in the EA group was 5.26, and the standard deviation was 3.11; the mean of HAMD-17 in the combined therapy group was 3.4. The standard deviation was 2.97. To reduce the error, the target sample size was slightly enlarged, and a 10% dropout rate was estimated. Therefore, a sample of 46 participants will be the goal for each group in the proposed trial. A total of 138 patients will be aimed for in total.

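### The planned between-group tests ignore the baseline score, although it is collected; adjusting for it is a nearly free gain in precision, and the change-score test keeps the sized 90% power only under inputs the article does not give

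*Protocol article*

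**What the plan says.** Statistical Analysis lists three kinds of between-group comparison. The first is on change: "Analysis of variance will be used to compare the mean changes between groups from baseline to each time point". The second is an independent-sample t-test, with no statement of whether it is applied to changes or to scores at a visit. The third is longitudinal: "Multiple measurements of the same indicator at different times will use repeated measures data analysis of variance". None is named as primary and none has the baseline score as a covariate. The only covariate mentioned is centre, and only if the subcentres reach inconsistent conclusions.

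Sample Size describes a one-way comparison: "Sample size estimation uses a completely random design to compare multiple sample means". The stated power and significance level are "1-β = 0.9, α = 0.05". The inputs come from an earlier study. For counselling the article reports that "the mean of HAMD-17 in the psychological counseling group was 5.7, and the standard deviation was 3.13". The corresponding figures are 5.26 (SD 3.11) for EA and 3.4 (SD 2.97) for combination therapy. With 10% dropout the target is 46 per group, 138 in all.

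Outcome Measures has HAMD-17 and BDI-II recorded before treatment and at weeks 2, 4 and 6. Table 1 (inclusion criteria) admits HAMD-17 scores from 7 to below 17.

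**The concern.** The sizing means all lie below the lowest score that a participant may have at entry, and the combination arm has the lowest of them. They therefore cannot be baseline scores, and they do not read as improvements. They are post-treatment levels, although the article does not label them so. The sample size thus uses the variance of a final score, while the stated analysis uses the variance of a change, and the two variances can differ in either direction.

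A change score also subtracts the whole baseline difference (a slope of 1), whatever the data's actual regression of final score on baseline. When the true slope is below 1, chance imbalance at baseline is over-corrected and precision is lost. At stake is some of the information from 138 participants and, under some inputs, the 90% power that the sample size claims.

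**Working it through.** **Inputs from the article.** Means 5.7, 5.26 and 3.4; SDs 3.13, 3.11 and 2.97; α = 0.05; 46 per group less 10% = 41.4, taken as 41 evaluable.

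**Assumed, because the article does not give them.** The correlation r between baseline and final HAMD-17, shown for 0.3, 0.4 and 0.5; and the baseline SD s₀, shown for 2.0, 2.5 and 2.87. The top value is that of an even spread over the ten integer scores 7 to 16: √((10² − 1)/12) = 2.87.

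**Step 1: reproduce the sample size.**
- Pooled variance = (3.13² + 3.11² + 2.97²)/3 = 9.43, so the final-score SD is s₁ = 3.07.
- Grand mean = 14.36/3 = 4.787. Sum of squared deviations = 0.913² + 0.473² + 1.387² = 2.981.
- Noncentrality at n = 41: 41 × 2.981/9.43 = 12.96, with 2 and 120 degrees of freedom. Power of the F test = 89.97%. At n = 42 it is 90.7%.
- 41/0.9 = 45.6, rounded up to 46; 42/0.9 = 46.7, rounded up to 47. The stated 46 is reproduced, for an unadjusted test of post-treatment scores.

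**Step 2: error variances.**
- Change score: s₁² + s₀² − 2·r·s₀·s₁.
- Baseline-adjusted (ANCOVA): s₁²(1 − r²), which does not depend on s₀.
- Example at r = 0.3, s₀ = 2.5: change = 9.43 + 6.25 − 2 × 0.3 × 2.5 × 3.071 = 11.07; ANCOVA = 9.43 × 0.91 = 8.58.

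**Step 3: break-even against the sizing.** The change score is noisier than the final score when s₀² > 2·r·s₀·s₁, that is, when r < s₀/(2·s₁):
- s₀ = 2.0: 2.0/6.14 = 0.33
- s₀ = 2.5: 2.5/6.14 = 0.41
- s₀ = 2.87: 2.87/6.14 = 0.47

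**Step 4: omnibus power with 41 per arm.** The power calculation of step 1 is repeated with each variance; ANCOVA gives up one degree of freedom. Information lost = 1 − (ANCOVA variance/change variance).

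| r | baseline SD | change-score variance | power, change score | power, ANCOVA | information lost |
|---|---|---|---|---|---|
| 0.3 | 2.0 | 9.75 | 88.9% | 92.6% | 12% |
| 0.3 | 2.5 | 11.07 | 84.4% | 92.6% | 23% |
| 0.3 | 2.87 | 12.38 | 80.0% | 92.6% | 31% |
| 0.4 | 2.0 | 8.52 | 92.8% | 94.5% | 7% |
| 0.4 | 2.5 | 9.54 | 89.6% | 94.5% | 17% |
| 0.4 | 2.87 | 10.62 | 86.0% | 94.5% | 25% |
| 0.5 | 2.0 | 7.29 | 96.0% | 96.5% | 3% |
| 0.5 | 2.5 | 8.00 | 94.2% | 96.5% | 12% |
| 0.5 | 2.87 | 8.85 | 91.8% | 96.5% | 20% |

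The ANCOVA variances are 8.58, 7.92 and 7.07 at r = 0.3, 0.4 and 0.5. Apart from the degree of freedom, ANCOVA is never the less precise of the two: the change variance exceeds the ANCOVA variance by (s₀ − r·s₁)², which cannot be negative.

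**The case against.** Several stronger readings are tempting, and the article does not support them.

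- **The trial is underpowered.** A reader might infer this from the mismatch between sizing and analysis. It does not follow. Above the break-even correlation the change-score test has more than the planned 90%, as every r = 0.5 row shows. Below it there is a shortfall, but the article gives no r, baseline SD or SD of change to say which case applies.
- **The break-even is r = 0.5.** That holds only if baseline and final SDs are equal. The entry window restricts baseline, which may lower r, but it also lowers the break-even. Citing only the first effect would overstate the loss.
- **The loss may reach 35%, with power of 77%.** This needs r = 0.3 and a baseline SD of 3.07, which is wider than an even spread over 7 to 16. Values nearer 2.0 are at least as natural under truncated entry, and there the gap is small.
- **The analysis is biased.** It is not. With randomised arms the change-score comparison estimates the same treatment difference.
- **The change-score ANOVA is the declared primary test.** The article names none. A t-test on week-6 scores would match the scale of the sizing. This does not rescue the plan, because that test is unadjusted too.

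It can also be said that covariates are usually left to an analysis plan, which is not shown here. That carries limited weight: the article commits to specific unadjusted tests, so the point concerns a stated choice and not a missing detail.

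**Conclusion.** The point stands as one of efficiency. Every between-group test of the scale scores that the article lists leaves out the baseline score, which will be on file anyway. For baseline SDs of 2.0 to 2.87 the change-score analysis forgoes about 12–31% of the information at r = 0.3, 7–25% at r = 0.4 and 3–20% at r = 0.5. A shortfall against the sized 90% is possible but conditional: it arises only if r is below roughly 0.33 to 0.47, depending on the baseline SD.

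This rests on reading the sizing means as post-treatment scores, on equal SDs across arms, on 41 evaluable per arm, and on assumed values of r and the baseline SD. The advantage of adjustment does not depend on knowing r. The figures are for HAMD-17 only; for BDI-II and the secondary scales the principle carries over, but the article gives nothing from which to compute the size.

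**What to change.** Make the between-group analysis of HAMD-17 at week 6 a linear model (ANCOVA) for the week-6 score with arm, baseline HAMD-17 and centre. Use the same model for BDI-II, SDS, SAS and PSQI, each with its own baseline. Include baseline as a covariate in the repeated-measures model, and keep mean changes as description. State this before any unblinded data are seen.

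The cost is one degree of freedom for baseline and three for the four centres, out of about 120, plus a change of wording. No further patients, visits or measurements are needed.

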### Trial Design

This study will be a multicenter, randomized, single blind clinical trial with three treatment groups (EA, counseling, and combination therapy). The flow chart in **Figure 1** shows more details regarding the clinical procedures. This study protocol has been approved by the Ethics Committee of the First Affiliated Hospital of Guangzhou University of Chinese Medicine, Affiliated Brain Hospital of Guangzhou Medical University, Guangdong Provincial Hospital of Chinese Medicine, and Guangdong Sanjiu Brain Hospital (NO. ZYYECK YJ [2019] 068).

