### Participants

Participants will be recruited by advertisement and doctor referrals from psychology department clinics. Interested individuals can contact research assistants by email or phone. A series of criteria and prerequisites will be sent to the prospective volunteers for filtering the most eligible subjects. First, registration information and pre-selection query forms with Self-rating Depression Scale (SDS), Pittsburgh Sleep Quality Index (PSQI), and Self-rating Anxiety Scale (SAS) will be sent to registered volunteers. Volunteers will be required to complete the form as a first-round selection prior to scheduling a first visit. This visit will further screen and evaluate a volunteer's eligibility according to inclusion criteria (**Table 1**). Research assistants will collect signed consent forms from volunteers who meet all prerequisites and agree to participate in the trial. Patients will not be included in the study if they meet one of the exclusion criteria (**Table 2**).

**Table 1 T1:** Inclusion criteria.

No	Item	Answer
1	18<age<55	□Yes
		□No
2	Presence of ≥ 1 but < 5 symptoms required for the diagnosis of major depression as detailed in the Diagnostic Statistical Manual of mental disorders (DSM-V), including loss of enjoyment/interest, marked tiredness or reduction of energy, agitation or psychomotor retardation, feelings of worthlessness or guilt, sleep disorders, reduced concentration, loss of appetite and body weight, loss of libido, recurrent suicidal thoughts;	□Yes
		□No
3	symptoms lasting at least 2 weeks	□Yes
		□No
4	BDI-II score≥14 points (24)	□Yes
		□No
5	HAMD-17 score: 7 points ≤ HAMD total score < 17 points (25)	□Yes
		□No

**Table 2 T2:** Exclusion criteria.

No	Item	Answer
1	Patients diagnosed with depression, previous mental illness, or organic mental disorders	□Yes
		□No
2	Patients suffering from serious diseases such as heart, brain, liver, kidney, or hematopoietic system disease	□Yes
		□No
3	Women during pregnancy and lactation or women of childbearing age who have fertility intentions	□Yes
		□No
4	Patients with depressive episodes caused by psychoactive substances and non-addictive substances	□Yes
		□No
5	Patients prescribed other drugs or therapies for treating depression during the trial	□Yes
		□No
6	Individuals addicted to alcohol or other drugs	□Yes
		□No
7	Patients with strong suicidal ideation	□Yes
		□No
8	Patients who are participating in other clinical trials at the same time	□Yes
		□No

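### Within-arm before-after paired t-tests are planned as significance tests, but with three active open-label arms selected on the outcome scales a significant fall is not evidence that an arm works

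*Protocol article*

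**What the plan says.** All of this is in the protocol article.

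- **Within-arm test.** Statistical Analysis: "The data before and after treatment in the group will be compared based on a paired" t-test.
- **Threshold.** Same section: two-tailed p "values < 0.05 will be considered as statistically significant". No test is exempted. The section mentions descriptive statistics for safety data but does not apply the label to the within-arm tests.
- **Between-arm tests.** Same section: "Analysis of variance will be used to compare the mean changes between groups from baseline to each time point", and "the comparison between groups will be performed using an independent sample" t-test. Repeated-measures analysis of variance is also listed.
- **Arms.** Trial Design: "single blind clinical trial with three treatment groups (EA, counseling, and combination therapy"). There is no untreated, waiting-list or sham arm.
- **Selection.** Table 1 under Participants requires "HAMD-17 score: 7 points ≤ HAMD total score < 17 points" and a BDI-II of at least 14. Outcome Measures names the same two scales as primary.
- **Blinding.** Only outcome evaluators and analysts are blinded; participants know their group.
- **Hypothesis.** Trial Objective: "We suspect that EA could alleviate the clinical symptoms of patients with sub-threshold depression as well as counseling". The same section then reasons that if acupuncture has no effect, the combination arm should do no better than counseling.

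**The concern.** A paired t-test asks whether the mean changed, not why. Three things other than treatment can lower the follow-up score here: the natural course of mild depressive symptoms over six weeks, expectation in participants who know what they receive, and regression to the mean after selection on the outcome scales. With no untreated arm, nothing inside one arm separates these from a treatment effect.

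The risk is practical. The Introduction cites a single-center trial in which EA, counseling and the combination each improved HAMD-17, with a control group for comparison, and presents this trial as the means to confirm that finding. This trial has no such control group. If EA and counseling each show a significant fall and do not differ significantly, it is easy to conclude that both work. The design does not support that conclusion.

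**Working it through.** **1. The plan's own figure.** Sample Size gives HAMD-17 means of 5.7 (counseling), 5.26 (EA) and 3.4 (combination), SDs of 3.13, 3.11 and 2.97, 90% power, alpha 0.05 and 10% dropout.

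- Pooled SD = √[(3.13² + 3.11² + 2.97²)/3] = 3.07.
- SD of the three means (divisor 3) = 0.997, so f = 0.997/3.07 = 0.325.
- One-way ANOVA (noncentral F) has power 0.8997 at 41 per group and 0.907 at 42.
- 41/0.90 = 45.6, which rounds up to the stated 46; starting from 42 gives 47.

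The stated size is therefore reproduced, and it was set for the between-arm comparison. Evaluable per arm: 46 × 0.90 ≈ 41.

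**2. Power of the pairwise contrasts at those means** (two-sided 0.05, unadjusted, 41 per arm). Standard error = 3.07 × √(2/41) = 0.678.

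| Contrast | Difference | Difference/SE | Power |
|---|---|---|---|
| EA vs counseling | 0.44 | 0.65 | about 10% |
| Combination vs EA | 1.86 | 2.74 | about 77% |
| Combination vs counseling | 2.30 | 3.39 | about 92% |

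The two add-on contrasts can be informative. EA against counseling is expected to be non-significant.

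**3. How small a fall the paired test calls significant.** Critical fall = t(0.975, 40) × SD of change/√41, with t = 2.021. The protocol gives no SD of change, so 3 to 5 is an assumption. Power is from the noncentral t.

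| SD of change | Critical fall | P(significant) for a 1-point non-treatment fall | For a 2-point fall |
|---|---|---|---|
| 3 | 0.95 | 55% | 99% |
| 4 | 1.26 | 35% | 88% |
| 5 | 1.58 | 24% | 71% |

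The size of any non-treatment fall is not in the protocol; 1 and 2 points are illustrations.

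**4. Regression to the mean on HAMD-17 alone, zero treatment effect.** Assumed: normal screened population with mean μ, SD 4.5 and retest correlation ρ. Expected fall = (1 − ρ) × (mean of those with 7 ≤ score < 17, minus μ). For μ = 6 and ρ = 0.6 the selected mean is 10.10, so the fall is 0.4 × 4.10 = 1.64. Simulated with 41 per arm:

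| Screened mean μ | Fall (ρ 0.8 to 0.6) | Significant improvement in one arm |
|---|---|---|
| 6 | 0.82 to 1.64 | 46% to 79% |
| 8 | 0.53 to 1.07 | 23% to 44% |
| 10 | 0.26 to 0.53 | 9% to 14% |
| 12 | 0 | about 2.5% (nominal in that direction) |

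The HAMD-17 window is two-sided with midpoint 12, so the effect vanishes when the screened mean lies there.

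**5. Both entry rules together, 46 per arm, zero treatment effect.** Assumed: screened means 6 to 10 (HAMD-17) and 12 to 18 (BDI-II), SDs 5 and 9, retest correlation 0.6 to 0.9, true-score correlation 0.6.

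- One arm significant: 4% to 57% on HAMD-17 and 10% to 70% on BDI-II, whose entry rule is a one-sided floor.
- All three arms significant together: 0% to 19% on HAMD-17 and 0% to 33% on BDI-II.
- Adding a HAMD-17 decline of 2 points shared by all arms (retest correlation 0.7, screened HAMD-17 means 8 to 10): 98% to 99.6% per arm, and 94% to 99% for all three.
- ANOVA of change between arms in the same simulations, with or without a shared decline: 4% to 6% false positives.

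The between-arm comparison removes the problem, because whatever all arms share cancels.

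**The case against.** The best defense is that the trial is comparative. Its objective, sample size and first-named efficacy analysis all concern differences between arms, and Trial Objective judges EA by combination against counseling, which is a randomized contrast. No sentence makes a paired test decisive. Ranking tests as primary or supportive may be left to an analysis plan that is not shown.

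Most of this stands, and it rules out several stronger readings that a reader might infer.

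- *That the paired tests are the only analysis bearing on EA.* They are not: combination against counseling estimates EA's effect as an add-on. What it does not estimate is EA given alone.
- *That three significant p-values will result.* Regression to the mean alone rarely makes all three arms significant under most of the assumptions above. A shared 2-point decline nearly always would, but the protocol gives no figure for natural course.
- *That a fall of at least 1.3 points (7 − 5.7) is built into every arm.* Sample Size does not say that its means are end-of-treatment values. If they are, they come from treated groups in another study and include any treatment effect.
- *That the objective claims equivalence of EA and counseling.* The wording may mean only that counseling also helps.

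The point about the analysis plan does not remove the concern. The test and its significance threshold are stated in the article, so this is a stated analysis and not a missing detail. The time effect in a repeated-measures analysis has the same limit as the paired test; only the group-by-time comparison is randomized.

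**Conclusion.** The concern holds in limited form. The plan tests before-after change within each arm at 0.05 in a design where that test cannot separate treatment from natural course, expectation or regression to the mean.

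The size rests on assumed values for the SD of change, retest correlation, screened mean and natural course. Across the ranges shown, the chance that an arm with no treatment effect is called significantly improved on HAMD-17 runs from the nominal 2.5% to near certainty. The between-arm tests are valid and already planned. They will probably leave EA against counseling unresolved, which is when a within-arm p-value is most likely to be used as evidence for EA alone. The documents do not show that the protocol intends to use it that way. The defect is an uninformative significance test with no limit on its interpretation, and the sample size is unaffected.

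**What to change.** In Statistical Analysis, replace the within-arm paired t-tests with the mean change and 95% CI for each arm, with no significance test and labelled descriptive. Add that effectiveness conclusions rest on the between-arm contrasts of change: combination against counseling for EA as an add-on, and combination against EA for counseling as an add-on. State, there and under Limitation, that without an untreated comparator the trial cannot show EA alone or counseling alone to be effective against no treatment.

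The cost is two or three sentences. Data collection, visits and the 46 per group are unchanged, because that number was computed for the between-arm comparison.
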